#### Secondary outcome

Secondary outcomes will be clinical complications and laboratory results serve as surrogate end-points for prognosis. The secondary outcomes include the following:The incidence of MACE (including heart failure, malignant arrhythmias, cardiogenic shock, cardiogenic death, and recurrent myocardial infarction) during hospitalization or at 30-day follow-upThe incidence of myocardial infarction-related mechanical complications during hospitalization or at 30-day follow-upThe difference between the trial groups in left ventricular ejection (LVEF) measured by echocardiography at baseline, 7th day, and 30th day

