### Outcome measurements

Hospitalized patients will be followed daily until the occurrence of a primary end-point event or discharge from the hospital. Telephone follow-up will be conducted on the 30th day after admission to understand the survival status of the patients. For patients who have been hospitalized for more than 30 days, end-point events will be collected on day 30 of hospitalization.

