### Follow-up

During the informed consent period, the researcher will have the patient consider whether they can complete the follow-up and then decide whether to participate in the study. In order to facilitate participant retention and complete follow-up, addresses and phone numbers of participants and their families will be collected after consent was obtained. In addition, we will request the physician in charge who is trusted by the patient to assist in the follow-up of the patient. The follow-up period will be divided into two phases, during hospitalization and after discharge. According to statistics, the average hospitalization time of patients with AMI in the First Affiliated Hospital of Shantou University Medical College was 10 days. During hospitalization, the staff will be scheduled to follow up daily, mainly to understand the occurrence of adverse events and the compliance of patients with medication, for a maximum of 30 days. Patients who have been hospitalized for less than 30 days will be followed up by phone or face-to-face on day 30, mainly to check the patient’s survival status and any readmission within 30 days. If there is a readmission within 30 days, further information on the reason for the admission and the presence of adverse cardiovascular events will be obtained. The detailed study schedule is listed in Table 1. Patients who completed the 30-day follow-up were considered to have met the clinical and trial requirements. Patients who discontinued the study drug prematurely will be marked as off-study drug/on study and will follow the same schedule of events as those patients who continue study treatment.

**Table 1 Tab1:** Timeline of trial procedures and follow-up schedule

Study period															
	Screening	Baseline	Follow-up												
Time point (days)	− 1	0	1	2	3	4	5	6	7	8	9	10	etc	30th	Close-out
Eligibility check	X	X													
Informed consent	X														
Relevant medical history taken	X	X													
Physical examination	X	X	X	X	X	X	X	X	X	X	X	X	X	X	
Full blood count		X							X			X		X	
Lipid levels		X							X			X		X	
Liver and renal function		X							X			X		X	
Myocardial enzymes		X							X			X		X	
C-reactive protein		X							X			X		X	
Pro-BNP		X							X			X		X	
HBALC		X							X			X		X	
Electrocardiogram		X							X			X		X	
Echocardiography		X							X			X		X	
All-cause death		X	X	X	X	X	X	X	X	X	X	X	X	X	X
MACE		X	X	X	X	X	X	X	X	X	X	X	X	X	X
Serious adverse events		X	X	X	X	X	X	X	X	X	X	X	X	X	X

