### Statistical and analytical plans

The analyses will adhere to intention-to-treat (ITT) principles. The ITT population included eligible patients who had been randomly assigned to participate in the study, regardless of whether any patients were taking a trial drug. Missing observations are accounted for using the predictive mean matching (PMM) method. Descriptive statistics will be used to analyze the results. Continuous data, such as age, height, and weight, will be presented as mean ± SD. Categorical data such as all-cause death, previous disease history, and smoking history will be expressed as frequency and percentage of patients in each category. Comparison baselines will be obtained using an independent sample *t* test. For the primary outcome, the chi-square test will be used to compare the all-cause mortality in both arms. Secondary outcomes will be assessed by the chi-square test for event rate, and the paired *T* test for quantitative secondary endpoints to compare both treatment arms. In addition, Kaplan–Meier curves will be calculated for visualizing the cumulative events in both groups during hospitalization. A *p*-value of less than 0.05 (*p* < 0.05) will be considered statistically significant. SPSS (25.0) will be used for statistical analysis.

The efficacy and safety of probiotics in the treatment of acute myocardial infarction are unknown. The purpose of interim analyses is to enable early detection of trial safety, early detection and termination of the study in the event of safety problems, and early detection of efficacy, which can be halted for efficacy if the trial is effective and has satisfied prespecified criteria. For interim analysis, we will do a group sequential statistical design with 2 interim analysis when we collect 33% (856) and 67% (1815) of the analyzable patients. The interim analysis will be performed using the Pocock method. Each analysis, including the final analysis, will be set at the same significance level alpha = 0.022 to maintain an overall significance level of 0.05. An independent Data Monitoring Committee supported by an independent, unblinded statistical center will regularly review safety data as well as the interim efficacy analysis.

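### Day-30 LVEF is a secondary outcome, but the follow-up text does not secure an echocardiogram for discharged patients, and the imputation rule as written would give an LVEF to patients who have died

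*Protocol article*

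**What the plan says.** All references are to the protocol article.

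- **Secondary outcome:** the arms are compared on LVEF "measured by echocardiography at baseline, 7th day, and 30th day".
- **Table 1** ("Timeline of trial procedures and follow-up schedule"): echocardiography is marked at baseline, day 7, day 10 and day 30. Physical examination, ECG and blood tests are also marked at day 30.
- **Outcome measurements:** "Telephone follow-up will be conducted on the 30th day after admission to understand the survival status of the patients". No visit is mentioned.
- **Follow-up:** "Patients who have been hospitalized for less than 30 days will be followed up by phone or face-to-face on day 30", and the purpose is "mainly to check the patient’s survival status and any readmission within 30 days". Echocardiography is not named. The same section reports that "the average hospitalization time of patients with AMI in the First Affiliated Hospital of Shantou University Medical College was 10 days".
- **Data collection and management:** ejection fraction appears among the admission parameters. The items named for day 30 are clinical events.
- **Statistical and analytical plans:** "The ITT population included eligible patients who had been randomly assigned to participate in the study", whether or not the drug was taken, and "Missing observations are accounted for using the predictive mean matching (PMM) method". No exception is stated for patients who died.

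**The concern.** There are two linked problems.

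First, the outcome and the table need the patient in front of an echocardiography machine on day 30, while the follow-up text is satisfied by a phone call. Site staff could follow that text exactly and collect no day-30 LVEF from a discharged patient. The values that were collected would then come from patients still in hospital, readmitted or willing to return, and in an open-label trial willingness to return could differ by arm.

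Second, a dead patient has no day-30 LVEF. A rule that fills every missing observation would give that patient a value taken from a living donor. If the probiotic reduces mortality as planned, this happens more often in the control arm, so the LVEF comparison would absorb a mortality difference without showing it.

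**Working it through.** **Planning figures.** The article gives no figure for missing LVEF, so the only figure to reproduce is the sample size that supplies the death rates. Inputs from the Sample size section: mortality 8.9% and 5.34%, two-sided alpha 0.05, 90% power, Freedman method, 15% dropout.

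- Hazard ratio = ln(1 − 0.0534) / ln(1 − 0.089) = 0.589.
- Freedman gives 157 events. 157 / (0.089 + 0.0534) = 1103 per arm, against 1102 stated.
- 1102 / 0.85 = 1297 per arm, as stated.

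The sample size reproduces and is not at issue here.

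**Expected deaths at those rates.**

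- Control: 1297 × 0.089 = 115.4.
- Probiotic: 1297 × 0.0534 = 69.3.
- Total: 184.7, about 185 of 2594 (7.1%), leaving about 2409 survivors.

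These are in-hospital rates, so any death between discharge and day 30 would add to them.

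**Share still in hospital on day 30.** The only input is the mean stay of 10 days.

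- Markov bound, with no distribution assumed: P(stay ≥ 30) ≤ 10/30 = 33%.
- Exponential stay (assumed): exp(−3) = 5.0%.
- Lognormal stay with SD 5 to 15 days (assumed): 0.5% to 6.0%.

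So at least two thirds of patients, and probably about 95%, have been discharged or have died by day 30.

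**Share with no day-30 LVEF.** Let d = 0.0712 be the share who died, h the share of survivors still in hospital, and f the share of discharged survivors examined in person. Applying the length-of-stay figures above to survivors is an approximation.

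Missing = 1 − (1 − d) × [h + (1 − h) × f]

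| h | f = 0 (phone only) | f = 0.5 | f = 1 (all attend) |
|---|---|---|---|
| 5% | 95.4% | 51.2% | 7.1% |
| 33% (Markov limit) | 69.0% | 38.1% | 7.1% |

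**When more than half are missing.** Setting missing to 0.5 gives f = (0.5/0.9288 − h) / (1 − h). This is 53.8% for h = 0, 51.4% for h = 5%, and 30.7% at the Markov limit. More than half the values are missing only if in-person attendance falls below that level. The article does not state f.

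**Imputation after death.** Under the literal rule, about 115/1297 = 8.9% of control values and 69/1297 = 5.3% of probiotic values at day 30 would be imputed for patients who had died. This holds even at f = 1.

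**The case against.** The strongest reply is that the plan already provides for a visit. Table 1 marks examination, blood tests, ECG and echocardiography on day 30, none of which can be done by phone. The Follow-up section permits face-to-face contact and gives the main purpose of the contact, not its only one. The call in Outcome measurements is tied to survival and does not exclude a separate visit. This stands in part. A reader might infer that day-30 contact is by telephone alone and that most day-30 LVEF values will therefore be missing and imputed. The documents do not support that, because it depends on an attendance share they never give. What remains is that no sentence requires a discharged patient to attend, and one section describes only a call.

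On imputation, a reader might infer that the plan explicitly intends to impute LVEF after death. It does not say so. There is one general sentence, and a separate analysis plan may limit it. The figure of 185 also assumes that the planned benefit is real. With no effect, expected deaths would be 2594 × 0.089 = about 231, equal by arm. The point still stands because the rule is stated here without qualification and, followed as written, gives values to patients who cannot have one.

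It might also seem natural to drop day 30 and make day 7 the LVEF endpoint, as matching the objective of measuring at baseline and after treatment. Treatment continues through the hospital stay, so for an average 10-day stay day 7 falls during treatment. The documents do not support that substitution as an obvious correction.

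**Conclusion.** The concern holds as an inconsistency about day-30 measurement and as an imputation rule that is too broad.

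- The Secondary outcome section and Table 1 require a day-30 echocardiogram, and the two follow-up descriptions do not secure one for discharged patients.
- The resulting loss lies between about 7% and about 95%. The upper figure assumes phone contact only and 5% of survivors still in hospital. Neither end is a forecast.
- About 185 patients (about 115 control, 69 probiotic) would receive an imputed LVEF after death under the literal rule. This rests on the planning mortality rates and on reading the PMM sentence without an unstated exception.

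The effect is confined to one time point of one secondary outcome. The primary mortality comparison is not touched by it.

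**What to change.** 1. Reconcile Outcome measurements, Secondary outcome, Follow-up and Table 1. Either state that the day-30 contact is the in-person visit with echocardiography that Table 1 already schedules, or, where contact is by phone only, report day-30 LVEF as available in those examined, with the number examined in each arm, and rely on the day-7 comparison already in the outcome.
2. Restrict PMM for LVEF to patients alive at the visit, and report deaths by arm alongside LVEF.

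**Cost.** This is a short wording amendment. It needs ethics and regulatory approval under Auditing and amendment, and the trial is recruiting. If the in-person option is chosen, patients who would otherwise only have been phoned must return.

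The day-30 comparison becomes one among survivors. If mortality differs by arm, survivors are no longer strictly comparable as randomised, which is why the deaths must appear beside it. The day-7 fallback has limits too: under the same assumed lognormal stays, only about 42% to 70% of patients would still be in hospital on day 7, so the number examined should be given there as well.

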#### Safety outcome

The safety outcomes will be occurrence of allergies, sepsis, and severe diarrhea/constipation.

### Definition

In this study, MACE is defined as heart failure, malignant arrhythmias, cardiogenic shock, cardiac death, and recurrent myocardial infarction.According to the AHA/ACC/HFSA Guidelines for Managing Heart Failure [15], the diagnosis of heart failure is mainly based on clinical manifestations and physical examination: (1) typical clinical manifestations of new-onset heart failure (such as dyspnea, ankle edema, fatigue), (2) moist rales could be heard in more than one-third of the lung fields, (3) chest X-ray showed non-cardiac pulmonary edema or pulmonary obstruction, and (4) abnormal levels of brain natriuretic peptide or B-type natriuretic peptide precursor.Malignant arrhythmias are defined as atrial fibrillation/flutter, ventricular tachycardia, and high-degreee atrioventricular block.The criteria for cardiogenic shock include less than 90 mmHg systolic blood pressure, continuing for at least 30 min, clinical signs of pulmonary congestion, and organ perfusion for signs of damage to at least one of the following performance: the mental state changes, skin and limbs cold and wet, oliguria, and urinate less than 30 ml per hour.Cardiac death is defined as death from any of several cardiac causes.Recurring myocardial infarction is defined as another myocardial infarction 28 days after the onset of acute myocardial infarction, with ST-elevation ≥ 1 mm recurs, or new pathogomonic Q waves appear in at least two contiguous leads, especially when accompanied by symptoms of ischemia.Myocardial infarction-related mechanical complications include cardiac rupture, ventricular septal rupture, and papillary muscle rupture.

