## Background

Acute myocardial infarction (AMI) is a severe form of coronary heart disease, and its high morbidity and mortality pose the main threat to human life and health. The incidence of adverse cardiovascular events after AMI, such as heart failure and arrhythmias, is associated with a substantially higher risk of death [1, 2]. In recent decades, with the rise of reperfusion therapy and the standardization of treatment for AMI, the mortality rate has decreased significantly. However, a significant inpatient mortality rate remains and can be as high as 8.9% [3], and the incidence of heart failure after acute myocardial infarction during hospitalization ranged from 40.2 to 40.5% [4]. Therefore, the treatment of acute myocardial infarction needs to be further optimized.

Recent studies have shown an important link between intestinal flora and the severity of myocardial infarction and heart repair after myocardial infarction [5, 6]. Intestinal disorders and bacterial translocations play an important role in the development of myocardial infarction and in cardiovascular events after infarction [7]. Patients with acute coronary syndrome (ACS) had typical intestinal microflora disorders, which were manifested as increased harmful bacteria and decreased beneficial bacteria [8]. Many animal studies have confirmed that probiotics can reduce the size of myocardial infarction and reduce cardiac hypertrophy [5, 9]. Several clinical trials have also reported that probiotics can reduce ventricular remodeling after MI and improve ventricular systolic function in patients with heart failure [10, 11], which imply that probiotic supplementation may improve the prognosis of acute myocardial infarction. However, it has not been reported whether probiotics can reduce the incidence of adverse cardiovascular events and mortality in patients with MI in the hospital. In this study, we will evaluate the effect of probiotics on in-hospital mortality and the incidence of major adverse cardiovascular events (MACE) in patients with AMI to understand whether probiotics have a protective effect on patients with acute myocardial infarction through a randomized controlled trial (RCT).

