### Data collection and management

At enrollment, we will collect demographic information of participants, including age, height, weight, blood pressure, heart rate, past medical history, smoking history, and laboratory parameters (including leukocytes, neutrophils, creatinine, uric acid, myocardial enzymes, lipid profile, pro-BNP, CRP, LEVF, LVd, LVS) at admission. Besides, death, heart failure, malignant arrhythmias, cardiogenic shock, recurrent myocardial infarction, and other conditions of patients will be recorded during the hospitalization or follow-up at the 30th day. Case report forms (CRFs) will be used to record all participant data. This task will be completed by the researchers, who will also enter the data into an electronic database by duplicate entry using the EpiData software (Denmark, version 3.1). All data will be stored in the scientific research platform of the First Affiliated Hospital of Shantou University Medical College, which is a secure server with limited access and supported for anonymity analysis and review.

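### The heart failure definition, a MACE component, lists four criteria without saying how many must be met, and its chest X-ray criterion is unscheduled and contradicts the condition

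*Protocol article*

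**What the plan says.** The Secondary outcome section counts heart failure as a component of MACE, during hospitalisation or at 30-day follow-up. The Definition section introduces it by saying that "the diagnosis of heart failure is mainly based on clinical manifestations and physical examination". Four numbered items follow. Item 1 is new symptoms, with breathlessness, swollen ankles and tiredness as examples. Item 2 and the start of item 3 read: "moist rales could be heard in more than one-third of the lung fields, (3) chest X-ray showed". The finding that the film must show completes item 3, which in full is: "chest X-ray showed non-cardiac pulmonary edema or pulmonary obstruction". Item 4 closes the list and brings in its joining word: "and (4) abnormal levels of brain natriuretic peptide or B-type natriuretic peptide precursor".

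The section does not say whether all, any one or some number of these are required, and item 4 has no threshold. Table 1 schedules physical examination and MACE capture daily, and pro-BNP at baseline and on days 7, 10 and 30. It has no row for chest X-ray. The Blinding section states that outcome assessors, investigators and caregivers all know the allocation. The Background reports that "the incidence of heart failure after acute myocardial infarction during hospitalization ranged from 40.2 to 40.5" per cent.

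**The concern.** An endpoint definition should let two people with the same record reach the same classification. This one does not, because the number of items required is left to the reader. One item also depends on an examination outside the study schedule, and that item names a finding opposite to the condition being defined.

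What is at stake is the MACE comparison. The Background figure suggests that heart failure may be one of the more frequent components. In an open-label trial, a loose rule leaves room for knowledge of the allocation to influence the classification or the decision to order a film. The primary outcome, all-cause mortality, is not affected.

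**Working it through.** The plan states no figure on this point, so the check sets the text side by side and applies each reading.

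**Does the wording settle the rule?** Two other places state a count where alternatives are meant: the AMI criteria under Inclusion criteria, and the organ-perfusion part of the cardiogenic shock definition, both of which ask for at least one of a list. The heart failure list has no such phrase, which favours requiring all four. Against that, the malignant arrhythmia definition, which comes next, uses 'and' to join alternatives. The text therefore does not decide between the readings, although all four is the more literal one.

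**What does each reading do?** The patients below are hypothetical. The last column applies the example rule given under the fix.

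| Patient | All four | Any one | Example rule |
|---|---|---|---|
| A: new dyspnoea, rales over half the lung fields, abnormal peptide, no film taken | not an event | event | event |
| B: as A, film taken and showing cardiac pulmonary oedema | not an event (film does not show the listed finding) | event | event |
| C: as A, film reported with the listed finding | event | event | event |
| D: no symptoms, no rales, abnormal peptide at a scheduled draw | not an event | event | not an event |
| E: fatigue only | not an event | event | not an event |

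A, B and C have the same symptoms, signs and peptide result. Under all four they are separated only by whether a film was taken and how it was reported, and B is excluded because the film supports heart failure. Under any one, D and E become events without any physical sign. Neither column matches a diagnosis resting mainly on symptoms and examination.

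**Can the loss under the all-four reading be sized?** Only by assumption. Let s be the share of true heart failure cases positive on each limiting item, with the items independent (both assumed).

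- All four items limiting, share counted = s^4: s = 0.9 gives 66%; 0.8 gives 41%; 0.7 gives 24%; 0.5 gives 6%.
- Only rales and X-ray limiting, share counted = s^2: s = 0.9 gives 81%; 0.8 gives 64%; 0.7 gives 49%; 0.5 gives 25%.
- Fewer than half are counted only if s is below 0.5^(1/4) = 0.841 in the first case, or below 0.5^(1/2) = 0.707 in the second.

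The documents give no value of s, and the plausible results fall on both sides of one half.

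**The case against.** The strongest reply is that the all-four rule is inferred. The lead-in describes what the diagnosis mainly rests on, the neighbouring definition uses 'and' for alternatives, and an intermediate rule may have been intended. This stands: the defect is that the rule is unstated, not that the protocol demonstrably demands all four.

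A second reply is that absence from Table 1 does not mean that no film is taken. Table 1 is not a full list of care; it also omits coronary angiography, which is one of the AMI criteria. A film can be ordered when heart failure is suspected, and an extra peptide measured. The item list under Data collection and management, "laboratory parameters (including leukocytes, neutrophils, creatinine, uric acid, myocardial enzymes, lipid profile, pro-BNP, CRP, LEVF, LVd, LVS) at admission", is baseline data and says nothing about how events are established. All of this stands. It leaves the film to unblinded clinical discretion, however, and does not repair the wording of item 3.

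A third reply is that the case report form or the full protocol may hold operational detail. That would excuse an omission, but here the article prints a definition, and the printed definition is ambiguous and in one item self-contradictory.

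A reader might go further and infer that most heart failure would fail to count as MACE, and that power on this outcome would fall sharply. The documents do not support that. It needs the all-four reading, positivity rates that are not given, independence between two signs of lung congestion that probably occur together, and an assumed treatment effect. The 40.2 to 40.5% comes from a cited source whose heart failure definition is not shown, so this trial's criteria cannot simply be applied to it. A missed case may also enter MACE through another component. Differential ordering of films by arm is a possibility, not something the documents show.

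**Conclusion.** The point holds as a badly fixed endpoint definition. The number of items required is not stated, the X-ray item is unscheduled and worded against the condition it should support, and the peptide item has no threshold. Both the all-four and the any-one reading misclassify recognisable patients. With unblinded assessors, the heart failure count, and with it MACE, can vary with the reader and with whether a film was ordered. The direction and size of the error cannot be derived from the documents; the percentages shown rest on assumed rates and serve only to show that. The issue concerns a secondary outcome. It should be corrected, but it does not threaten the primary comparison.

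**What to change.** State one combination rule for the endpoint. An example is new-onset symptoms or signs of heart failure after randomisation, plus at least one objective item: rales to the stated extent, pulmonary congestion on X-ray where a film was taken, or a natriuretic peptide above a prespecified threshold. No patient then fails only because no film exists, and no single laboratory value qualifies.

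In the same amendment:

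- correct the non-cardiac wording, and clarify what pulmonary obstruction means in item 3;
- apply the same rule to in-hospital events and to readmissions up to day 30, using the readmission record, since day-30 contact may be by telephone;
- re-apply the rule identically in both arms to events already recorded.

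The rule concerns endpoint classification only. It adds no procedure and does not change patient care.

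The cost is a short change to the definition and the case report form, and a second review of events already coded. The downside is that a broader rule may admit some milder heart failure, such as fatigue with a raised peptide, so the peptide threshold should be chosen with that in mind.

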## Methods

### Study design

This prospective trial will be a single-center, open-label, randomized, controlled, superiority clinical trial. A total of 2594 patients with AMI (both acute ST-segment elevation and non-ST-segment elevation myocardial infarction) will be recruited and randomized in a 1:1 fashion to one of the two treatment arms from October 2020 through October 2025. The protocol was designed according to the Standard Protocol Items: Recommendations for Interventional Trials (SPIRIT) 2013 Statement [12]. The protocol was designed in accordance with the SPIRIT 2013 Statement (Standard Protocol Items: Recommendations for Interventional Trials). The SPIRIT Checklist for this protocol is detailed in the Supplementary Material, Additional file 2.

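### Recurrent infarction counts only from 28 days after onset, but MACE is collected only to day 30 after admission, so the component misses most reinfarctions in follow-up

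*Protocol article*

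**What the plan says.** All references are to the protocol article.

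- **Definition**, on the composite: "MACE is defined as heart failure, malignant arrhythmias, cardiogenic shock, cardiac death, and recurrent myocardial infarction". On the component: "Recurring myocardial infarction is defined as another myocardial infarction 28 days after the onset of acute myocardial infarction". The sentence goes on to require either renewed ST elevation of at least 1 mm or new Q waves in two or more adjoining leads. Ischaemic symptoms are mentioned as supportive.
- **Secondary outcome** counts MACE in hospital or at the 30-day follow-up.
- **Outcome measurements** sets the end of observation: "Telephone follow-up will be conducted on the 30th day after admission", and for longer stays "For patients who have been hospitalized for more than 30 days, end-point events will be collected on day 30 of hospitalization".
- **Follow-up** treats day 30 as completion ("Patients who completed the 30-day follow-up were considered to have met the clinical and trial requirements") and gives the usual stay: "the average hospitalization time of patients with AMI in the First Affiliated Hospital of Shantou University Medical College was 10 days". Table 1 marks MACE at baseline and at each follow-up point to day 30. Its only later column is an undated close-out.
- **Data collection and management**: "recurrent myocardial infarction, and other conditions of patients will be recorded during the hospitalization or follow-up at the 30th day".
- **Study design** enrols "both acute ST-segment elevation and non-ST-segment elevation myocardial infarction". **Inclusion criteria** diagnose the index event by a biomarker above the 99th percentile plus any one of four conditions: symptoms, ECG, echocardiography, or thrombus at angiography or autopsy.

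The article gives no other definition of recurrent infarction.

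**The concern.** The component opens at about the time observation closes. A reinfarction in the first four weeks is looked for but does not meet the definition. Fewer recurrent infarctions is part of the stated secondary objective, so a component that can count only the last few days cannot answer that part of it.

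The wording also leaves room for different readings. A site might take it as on or after day 28, or as a slip for within 28 days, and the two readings count almost complementary sets of events. Under Blinding, outcome assessors and data analysts know the allocation, so a choice made case by case would be made with the arm known.

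The ECG requirement narrows the component further. A reinfarction diagnosed by biomarker and symptoms, or by biomarker and a new wall-motion abnormality, would satisfy the conditions used for the index event. It would still fail here if it showed neither ST elevation nor new Q waves.

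**Working it through.** The plan gives no figure for reinfarction, so there is none to reproduce on this point. The sample size rests on mortality alone. HR = ln(1 − 0.0534)/ln(1 − 0.089) = 0.589; the Freedman method at 90% power and two-sided 0.05 gives 157 events; 157/(0.089 + 0.0534) = 1102.5 per arm, against the stated 1102. Recurrent infarction does not enter it.

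**Inputs from the article.** Earliest qualifying time: 28 days from onset. End of observation: day 30 from admission. Average stay: 10 days.

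**Assumptions.** The definition is read as day 28 or later. The article gives no delay from onset to admission, so d = 0 to 3 days is used. The hazard shapes and stay distributions below are also assumed.

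**Step 1: countable window.** Observation ends 30 + d days after onset, so the window is (30 + d) − 28 = 2 + d days. Under a constant hazard the share counted is (2 + d)/30.

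| Delay d (days) | Countable days | Share counted | Share excluded |
|---|---|---|---|
| 0 | 2 | 6.7% | 93.3% |
| 1 | 3 | 10.0% | 90.0% |
| 2 | 4 | 13.3% | 86.7% |
| 3 | 5 | 16.7% | 83.3% |

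Counting calendar days inclusively with d = 0 gives 3 of 31, or 9.7%.

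**Step 2: declining hazard, d = 0.** With λ = ln 2/half-life, the share counted is (e^(−28λ) − e^(−30λ))/(1 − e^(−30λ)).

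| Assumed half-life (days) | Share counted | Share excluded |
|---|---|---|
| 30 | 4.7% | 95.3% |
| 14 | 3.0% | 97.0% |
| 7 | 1.2% | 98.8% |
| 3 | 0.1% | 99.9% |

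**Step 3: the index stay.** A patient discharged at the average 10 days cannot have a qualifying event before discharge. With mean 10, P(stay > 28 days) is:

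- exponential: e^(−2.8) = 6.1%
- gamma, shape 2: e^(−5.6)(1 + 5.6) = 2.4%
- gamma, shape 4: e^(−11.2)(1 + 11.2 + 11.2²/2 + 11.2³/6) = 0.4%

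This describes the in-hospital part only; events after discharge can still be picked up at day 30.

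**Step 4: the other reading.** If the sentence meant within 28 days, the window with d = 0 would be 28/30 = 93.3% of follow-up, against 6.7% as written.

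**The case against.** The strongest reply is that this is a dropped word. MACE is marked daily in Table 1, recurrent infarction is recorded in hospital and at day 30, and reasons for readmission are collected. That pattern fits an intention to count early events. The slip is plausible, but nothing in the article confirms it, and the definition as it stands governs the count.

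A second reply is that little depends on it. Much of this stands. Recurrent infarction is one of five components of a secondary outcome. Background cites in-hospital heart failure of 40.2% to 40.5%, so other components are likely to dominate MACE. An early reinfarction followed by heart failure, shock, malignant arrhythmia or cardiac death still counts through that component.

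Three stronger readings are tempting and are not supported:

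- A reader might infer that the MACE rate is materially understated. The article gives no reinfarction rate and no overlap between components, so the effect on total MACE cannot be computed.
- A reader might infer that any effect on reinfarction is invisible. The events may still be recorded; what fails is their classification under the definition.
- A reader might infer that no non-ST-elevation reinfarction can count. One with new Q waves qualifies; only an event with neither ECG change is lost. The phrase about another infarction may also be read as carrying the biomarker requirement over from the inclusion criteria, which makes the ECG condition an added restriction rather than a replacement.

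**Conclusion.** The definition conflicts with the trial's own observation window and needs correction. Taken as written, 2 to 5 of about 30 days are countable for delays of 0 to 3 days, and roughly 83% to 93% of reinfarctions in the window are excluded under a constant hazard. The excluded share is higher if the hazard declines. Only about 0.4% to 6% of patients would still be in hospital at day 28, given the assumed stay distributions. The delays, hazard shapes and stay distributions are assumptions; the 28-day, 30-day and 10-day figures are the article's.

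The ECG requirement is a second, smaller restriction in the same sentence, and correcting the timing alone would leave it in place.

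The consequence is a recurrent-infarction result that cannot be interpreted within a secondary composite. A reader might go further and doubt the primary result or the trial's power. Neither follows, since both rest on all-cause death.

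**What to change.** Replace the sentence in the Definition section so that it agrees with Outcome measurements, Secondary outcome and Follow-up. Recurrent infarction would be any new infarction, distinct from the index event, from randomisation through day 30 after admission. It would require a new biomarker rise together with at least one of the four conditions listed under Inclusion criteria.

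The new rise has to be written in as an addition. The inclusion criteria ask only for a value above the 99th percentile, which may still be elevated from the index infarction and would not by itself identify a second event.

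Apply the definition identically in both arms, and settle it before outcomes are compared by arm. This matters more than usual because assessors and analysts are unblinded.

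The cost is one amended definition, plus a source-record check for events that sites did not record because of the current wording. That check may be incomplete: Table 1 schedules myocardial enzymes and ECG only at baseline and days 7, 10 and 30, and some discharged patients are followed by telephone. Some early events may therefore depend on ward or readmission records.
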